7. It is intended to measure the numbers of MenC specific memory B cells in the blood at 5 months, 12 months, 6 days following the 12 month booster dose, at 13 months and 24 months on a subset of participants. Specific memory B cells against diphtheria and tetanus will also be measured and used as a control. As many participants as possible would be included in this subset but the number would be determined by the practicalities of getting the blood to the laboratory in time (before midday) for processing.

8. To assess the local and systemic adverse reactions experienced by participants in the four different study groups after immunisation with each dose of the MenC-CRM197, MenC-TT and Hib-MenC vaccines.

Alternating limb component

1. To compare the *S. pneumonia*e IgG GMCs and percentage of infants with serum concentration of *S. pneumonia*e specific IgG ≥0.35 g/ml for all 13 PCV13 serotypes at 5, 12, 13 and 24 months of age in children receiving PCV13 in a consistent limb (subgroups ‘a’) vs those receiving this in alternating limbs (subgroups ‘b’).
2. To compare serotype specific pneumococcal B cell phenotype in a subset of participants at 5, 12, 13 and 24 months of age in children receiving PCV13 in a consistent limb (sub groups ‘a’) vs those receiving this in alternating limbs (subgroups ‘b’).

3. To compare the anti-PRP IgG GMCs and percentage of infants with serum concentration of anti-PRP IgG ≥0.15g/ml and ≥1.0 g/ml and at 5, 12, 13 and 24 months of age in children receiving DTaP-IPV-Hib in a consistent limb (sub groups ‘a’) vs those receiving this in alternating limbs (subgroups ‘b’).

4. To compare the anti-tetanus toxoid GMCs and percentage of infants with anti-tetanus toxoid >0.1 IU/ml at 5,12, 13 and 24 months of age in children receiving DTaP-IPV-Hib in a consistent limb (sub groups ‘a’) vs those receiving this in alternating limbs (subgroups ‘b’)

5. To compare the local or systemic vaccine reactions in subgroups a and b at each vaccination time point.

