***Single dose MenC-CRM197 Group n=160**

MenC-CRM197 at 3 months

Visit 5

Visit 6**

Visit 7

Hib-MenC boost + PCV13 at 12 months

VP

VP

VP

VP

*Control group n=64

Visit 2

Visit 3

MMR

Visit 8

VP

*Single dose MenC-TT Group n=114 MenC-TT at 3 months

*Participants would be randomised to receive MenC-CRM197 at 3 and 4 months (Two Dose MenC Group), or a single dose at 3 months (Single Dose MenC-CRM197 Group) or a single dose of MenC-TT at 3 months (Single dose MenC-TT Group) or no priming doses (Control Group). All participants will receive the DTaP-IPV-Hib vaccine at 2, 3 and 4 months and the PCV13 at 2 and 4 months according to the UK immunisation schedule. All participants would be boosted with the Hib-MenC vaccine and the booster dose of PCV13 at 12 months and will receive the MMR vaccine at 13 months.

Venepuncture (VP), taking 5 ml of blood, will be performed at 5 months (Visit 4), and taking 7.5ml of blood will be performed at 12 months (Visit 5), 12 months+6 days (Visit 6), at 13 months (Visit 7) and at 24 months (Visit 8). Two attempts may be made to obtain a blood sample at each visit, if the parent gives verbal consent at the time of the procedure for a second attempt. If no blood is obtained, a second visit may be made if the parent agrees to this.

** Visit 6 will be performed on all participants in the control group and a subset of 64 participants in the Two Dose MenC, Single Dose MenC-CRM197 and Single Dose MenC-TT groups (as determined by randomisation at enrolment, see section 6.4.4)

In addition, participants will be randomised at enrolment to receive PCV13 and DTaP-IPV-Hib in either consistent limbs (subgroup a) or alternating limbs (subgroup b) as follows

| **Subgroup a**  (Consistent limbs) | **Subgroup b**  (Alternating limbs) |
| --- | --- |
| DTaP-IPV-Hib in right leg at 2, 3 and 4 months  PCV13 in right leg at 2, 4and 12 months | DTaP-IPV-Hib in left leg at 2 months and in right leg at 3 and 4 months*  PCV13 in left leg at 2 months, right leg at 4 months and left arm at 12 months |

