2. Serotype specific pneumococcal B cell phenotype in a subset of participants at 5, 12, 13 and 24 months of age in children receiving PCV13 in a consistent limb (sub groups ‘a’) vs those receiving this in alternating limbs (subgroups ‘b’).

3. Anti-PRP IgG GMCs or percentage of infants with serum concentration of anti-PRP IgG ≥ 0.15 g/mL and ≥1.0 g/ml at 5, 12, 13 and 24 months of age in children receiving DTaP-IPV-Hib in a consistent limb (sub groups ‘a’) vs those receiving this in alternating limbs (subgroups ‘b’).

4. Anti-tetanus toxoid GMCs or percentage of participants with anti-tetanus toxoid >0.1IU/ml at 5, 12, 13 and 24 months of age in participants in receiving DTaP-IPV-Hib in a consistent limb (sub groups ‘a’) vs those receiving this in alternating limbs (subgroups ‘b’).

*Reactogenicity*

The following comparisons would be performed to assess differences between:

Local adverse events

1. The percentage of infants with each type of adverse event, and at least one adverse event for local adverse events after one dose of MenC-CRM197 at 3 months (Single Dose MenC-CRM197 Group) vs the second dose of MenC-CRM197 at 4 months (Two Dose MenC Group).
2. The percentage of infants with each type of adverse event, and at least one adverse event for local adverse events after one dose of MenC-CRM197 at 3 months (Single Dose MenC-CRM197 Group) vs one dose of MenC-TT at 3 months (Single Dose MenC-TT Group).
3. The percentage of infants with each type of adverse event, and at least one adverse event for local adverse events after each dose of DTaP-IPV-Hib (at 2, 3 and 4 months) and PCV13 (at 2 and 4 months) in the consistent limb group (sub groups ‘a’) vs. the alternating limb group (subgroups ‘b’).
4. The percentage of infants with each type of adverse event, and at least one adverse event for local adverse events after the 12 month booster MenC and PCV13 vaccination in the
   1. Two Dose MenC Group vs 0 Dose Control Group
   2. Single Dose MenC-CRM197 Group vs. 0 Dose Control Group
   3. Single Dose MenC-TT Group vs. 0 Dose Control Group
   4. Single Dose MenC-CRM197 Group vs. Two Dose MenC Group
   5. Single Dose MenC-CRM197 Group vs Single Dose MenC-TT Group
   6. the consistent limb group vs. the alternating limb group

Systemic adverse events

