**C) Analysis of safety**

The data summaries will report the total number and percentage of infants experiencing each type of adverse event, and the total number and percentage of infants experiencing at least one adverse event of any type, for each dose group, and the total number of infants in each dose group, for local and general adverse events during the 4-day follow-up period after each MenC (including Hib-MenC), DTaP-IPV-Hib and PCV13 vaccination. The classification of severity of local adverse events and fever will follow the Brighton collaboration guidelines 35 - 38.

Where the adverse event is further classified with a grade (1, 2, 3) related to severity, the summary reports will include the numbers in each class.

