**Local adverse events**

1. percentage of infants with each type of adverse event, and at least one local adverse event after each dose of MenC vaccine (at 3 and 4 months)
   1. Single dose MenC-CRM197 Group vs. Two dose MenC Group
   2. Single Dose MenC-CRM197 Group vs Single Dose MenC-TT Group
2. percentage of infants with each type of adverse event, and at least one local adverse event after each dose of DTaP-IPV-Hib (at 2, 3 and 4 months) and PCV13 (at 2 and 4 months)
   1. the consistent limb group vs. the alternating limb group
3. percentage of infants with each type of adverse event, and at least one local adverse event after the 12 month booster Hib-MenC and PCV13 vaccination
   1. Two dose MenC Group vs. 0 dose control Group
   2. Single dose MenC-CRM197 Group vs. 0 dose control Group
   3. Single dose MenC-CRM197 Group vs. Two dose MenC Group
   4. Single dose MenC-TT Group vs 0 dose control Group
   5. Single dose MenC-CRM197 Group vs Single dose MenC-TT Group
   6. the consistent limb group vs. the alternating limb group

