# APPendix a: study flow CharT

| **Details of vaccine administration for each treatment group** | | | **Visit 1** | **Visit 2** | **Visit 3** | **Visit 4** | **Visit 5** | **Visit 6*** | **Visit 7** | **Visit 8** |
| --- | --- | --- | --- | --- | --- | --- | --- | --- | --- | --- |
|  |  |  | **Blood** | **Blood** | **Blood** | **Blood** | **Blood** |
| **Two Dose MenC Group**  **(2 doses MenC-CRM197)**  **Group 2** | **a** | Right leg | DTaP-IPV-Hib  PCV13 | DTaP-IPV-Hib | DTaP-IPV-Hib  PCV13 |  | PCV13 |  | MMR |  |
| Left leg |  | *MenC****-CRM197*** | *MenC****-CRM197*** |  | Hib-MenC |  |  |
| **b** | Right leg |  | DTaP-IPV-Hib | DTaP-IPV-Hib  PCV13 |  |  |  | MMR |  |
| Left leg/ arm | DTaP-IPV-Hib  PCV13 | *MenC***-*CRM197*** | *MenC****-CRM197*** |  | Hib-MenC (leg), PCV13 (arm) |  |  |
| **Single Dose MenC-CRM197 Group**  **(1 dose MenC-CRM197)**  **Group 1** | **a** | Right leg | DTaP-IPV-Hib  PCV13 | DTaP-IPV-Hib | DTaP-IPV-Hib  PCV13 |  | PCV13 |  | MMR |  |
| Left leg/ arm |  | *MenC***-*CRM197*** |  |  | Hib-MenC |  |  |
| **b** | Right leg |  | DTaP-IPV-Hib | DTaP-IPV-Hib  PCV13 |  |  |  | MMR |  |
| Left leg/ arm | DTaP-IPV-Hib  PCV13 | *MenC****-CRM197*** |  |  | Hib-MenC (leg) PCV13 (arm) |  |  |
| **Control Group**  **(0 dose MenC priming)**  **Group 3** | **a** | Right leg | DTaP-IPV-Hib  PCV13 | DTaP-IPV-Hib | DTaP-IPV-Hib  PCV13 |  | PCV13 |  | MMR |  |
| Left leg/ arm |  |  |  |  | Hib-MenC |  |  |
| **b** | Right leg |  | DTaP-IPV-Hib | DTaP-IPV-Hib  PCV13 |  |  |  | MMR |  |
| Left leg/ arm | DTaP-IPV-Hib  PCV13 |  |  |  | Hib-MenC (leg) PCV13 (arm) |  |  |
| **Single Dose MenC-TT Group**  **(1 dose MenC-TT)**  **Group 4** | **a** | Right leg | DTaP-IPV-Hib  PCV13 | DTaP-IPV-Hib | DTaP-IPV-Hib  PCV13 |  | PCV13 |  | MMR |  |
| Left leg/ arm |  | *MenC-TT* |  |  | Hib-MenC |  |  |
| **b** | Right leg |  | DTaP-IPV-Hib | DTaP-IPV-Hib  PCV13 |  |  |  | MMR |  |
| Left leg/ arm | DTaP-IPV-Hib  PCV13 | *MenC-TT* |  |  | Hib-MenC (leg) PCV13 (arm) |  |  |

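### The 12-month local-reaction outcome is worded jointly for Hib-MenC and PCV13; it should be split by injection site before it serves the MenC dose-group contrasts

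*Protocol*

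**What the plan says.** Protocol section 9.1 C, under Local adverse events, item 3, names one booster outcome: each type of event, and "at least one local adverse event after the 12 month booster Hib-MenC and PCV13 vaccination". Six comparisons hang on it: five between MenC dose groups, and consistent versus alternating limb. Section 6.2, local item 4, carries the same joint wording: "at least one adverse event for local adverse events after the 12 month booster MenC and PCV13 vaccination in the". Neither place lists an outcome for the Hib-MenC site alone or the PCV13 site alone.

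The infant-phase items in 9.1 C are built differently. Item 1 is tied to the MenC vaccine, "at least one local adverse event after each dose of MenC vaccine (at 3 and 4 months"), and carries only dose-group contrasts. Item 2 covers DTaP-IPV-Hib and PCV13 and carries only the limb contrast.

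The objectives are in section 5.2. Objective 8 of the MenC component concerns reactions by study group "after immunisation with each dose of the MenC-CRM197, MenC-TT and Hib-MenC vaccines". Objective 5 of the limb component is "To compare the local or systemic vaccine reactions in subgroups a and b at each vaccination time point".

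On sites, section 6.1 gives subgroup a "PCV13 in right leg at 2, 4and 12 months", and Appendix A lists Hib-MenC on the left for that subgroup. For subgroup b, Appendix A shows "Hib-MenC (leg), PCV13 (arm"). The descriptive summaries in 9.1 C are worded per vaccination: "after each MenC (including Hib-MenC), DTaP-IPV-Hib and PCV13 vaccination".

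**The concern.** The dose-group contrasts at 12 months should show whether earlier MenC doses change the local reactogenicity of the Hib-MenC booster. Every child also receives PCV13 at that visit, on the same schedule in all four dose groups. If one binary outcome covers both injections, a child with a reaction only at the PCV13 site counts as an event whatever happened at the Hib-MenC site. Such events add to both sides of a dose-group contrast and can mask a real difference.

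For a safety outcome this is the unhelpful direction. A finding of similar booster reactogenicity after zero, one or two priming doses could come partly from the way the outcome was built. Joint wording suits the systemic items, because a systemic event cannot be assigned to a site. A local event can.

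**Working it through.** **The plan's own figure.** There is none to reproduce. The protocol gives no rate, effect size or power for any local-reaction outcome.

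**Does the wording pool the sites?** In the infant phase, the MenC item serves the dose-group contrasts and the DTaP-IPV-Hib and PCV13 item serves the limb contrast. The booster item drops this separation: one outcome naming both vaccines serves both factors. A single pooled outcome is the natural reading, although no rule says so.

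**Inputs.** Section 9.2 gives 160 infants in each of the Two Dose and Single Dose MenC-CRM197 groups and 64 in the Control group, with 12.5% drop-out: 160 × 0.875 = 140 and 64 × 0.875 = 56. Section 9.1 C reports an odds ratio and a risk difference with 95% confidence intervals. All reaction rates below are assumptions.

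**Formula.** Let h be the Hib-MenC-site rate in a dose group and c the PCV13-site rate, taken as equal in all dose groups and independent of h within a child.

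- Either-site rate: u = 1 − (1 − h)(1 − c)
- Pooled risk difference: u1 − u0 = (h1 − h0)(1 − c)

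**Example.** Take h1 = 0.35 and h0 = 0.20. At c = 0.20, u1 = 1 − 0.65 × 0.80 = 0.48 and u0 = 1 − 0.80 × 0.80 = 0.36. The difference is 0.12 and the odds ratio is (0.48/0.52)/(0.36/0.64) = 1.64. Power is for a two-sided 5% test of two proportions by normal approximation.

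| PCV13-site rate c | Rates compared | Risk difference | Odds ratio | Power, 140 v 140 | Power, 140 v 56 |
|---|---|---|---|---|---|
| 0 (Hib-MenC site alone) | 0.35 v 0.20 | 0.15 | 2.15 | 81% | 54% |
| 0.20 | 0.48 v 0.36 | 0.12 | 1.64 | 53% | 33% |
| 0.40 | 0.61 v 0.52 | 0.09 | 1.44 | 33% | 21% |
| 0.60 | 0.74 v 0.68 | 0.06 | 1.34 | 20% | 14% |

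**Sensitivity to the assumptions.**

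- *Correlated sites.* With a within-child correlation of 0.4 and the same Hib-MenC rates, the risk difference is 0.108 at c = 0.20 and 0.075 at c = 0.40. The odds ratios are 1.61 and 1.35. The direction is unchanged.
- *Nested reactions.* If PCV13-site reactions occurred only in infants who also reacted at the Hib-MenC site, then u = h and nothing is diluted.
- *PCV13 rate differing by dose group.* If it were 0.30 in the first group and 0.20 in the second, the pooled rates would be 1 − 0.65 × 0.70 = 0.545 and 0.36. The difference of 0.185 is larger than 0.15, so the shrinkage depends on the equal-rate assumption.

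**The case against.** The strongest reply is that no text says a reaction at either site makes an event. The item joins two vaccines with a conjunction, as the infant DTaP-IPV-Hib and PCV13 item does. Read beside the per-vaccination descriptive summaries in 9.1 C, it could be shorthand for two vaccine-specific analyses, with the derivation left to a statistical analysis plan. This stands in part. Pooling is an inference, and the summaries would still let a Hib-MenC-specific difference be seen. But the protocol itself sets the outcome and its contrasts in two places, and the wording allows two different analyses. In an unblinded trial that choice is better closed before the data are seen.

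Second, a reader might infer that PCV13-site reactions are unrelated to MenC priming and that every dose-group contrast is therefore diluted by a known amount. The documents do not support that. The same PCV13 schedule in all groups makes equal rates plausible, but the protocol does not address the point and gives no rates.

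Third, objective 8 speaks of reactions after each dose and names no site. Any local reaction at a visit where both boosters are given is a fair measure of tolerability. That justifies keeping an any-site summary. It does not make any-site the best outcome for a question about Hib-MenC.

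Fourth, the limb contrast should not be confined to the PCV13 site. Limb objective 5 covers vaccine reactions at every vaccination time point, so Hib-MenC-site reactions belong there too. This stands in full and shapes the fix.

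**Conclusion.** The point holds as a defect in how a secondary safety outcome is worded. The most natural reading is one pooled outcome, which matches objective 8 poorly although Appendix A makes attribution by site possible.

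Dilution follows on two conditions: the item is analysed as any local event at either site, and PCV13-site reactions do not differ by dose group. Both the risk difference and the odds ratio then move toward no difference, apart from the extreme case of nested reactions. The factor of one minus the PCV13-site rate also needs independence between sites. The table illustrates that mechanism under assumed rates and does not estimate what this trial would lose. The protocol makes no power claim for reactogenicity and sets no margin for concluding similarity, so no stated aim is shown to fail.

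The documents do not support saying that the plan definitely pools the sites, or that its dose-group contrasts are biased by a particular amount. The primary endpoint, its margin and the sample size are untouched.

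**What to change.** Reword section 9.1 C local item 3 and section 6.2 local item 4 so that the booster outcome is defined by vaccine and injection site:

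- local reactions at the Hib-MenC site, for the five MenC dose-group contrasts;
- local reactions at the PCV13 site and, separately, at the Hib-MenC site, for the limb contrast, in line with limb objective 5;
- local reactions at any site, as an additional summary.

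The systemic items can stay joint. The cost is small: for each event type there are seven comparisons (five dose-group and two limb) in place of six, plus the any-site summary. No new visits or participants are needed. The change assumes that the diary cards record local reactions by site, as the per-vaccination summaries imply; this should be confirmed.

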**Systemic adverse events**

1. percentage of infants with each type of adverse event, and at least one systemic adverse event after MenC (3 and 4 months), DTaP-IPV-Hib (2, 3 and 4 months) and PCV13 (2 and 4 months) vaccination
   1. Two dose MenC Group vs. 0 dose control Group
   2. Single dose MenC-CRM197 Group vs. 0 dose control Group
   3. Single dose MenC-CRM197 Group vs. Two dose MenC Group
   4. Single dose MenC-TT Group vs 0 dose control Group
   5. Single dose MenC-CRM197 Group vs Single dose MenC-TT Group
   6. the consistent limb group vs. the alternating limb group
2. percentage of infants with each type of adverse event, and at least systemic one adverse event after the 12 month booster Hib-MenC and PCV13 vaccination
   1. Two dose MenC Group vs. 0 dose control Group
   2. Single dose MenC-CRM197 Group vs. 0 dose control Group
   3. Single dose MenC-CRM197 Group vs. Two dose MenC Group
   4. Single dose MenC-TT Group vs 0 dose control Group
   5. Single dose MenC-CRM197 Group vs Single dose MenC-TT Group
   6. The consistent limb group vs. the alternating limb group

## 9.2 The Number of Participants

This is a non-inferiority trial assessing whether there is any difference in the antibody level between infants who receive no priming doses of MenC and those who receive 1 priming dose or 2 priming doses of MenC-CRM197.

The total sample size for the study is 498 participants randomised on a 10:10:7:4 basis to the 4 study groups. This will result in 160 participants in the Two Dose MenC group, 160 in the Single Dose MenC-CRM197 group, 114 in the Single Dose MenC-TT group, and 64 in 0 dose MenC (Control) group. Based on a mean (SD) log SBA of 3.47 (0.9) at 1 month after booster for 2 dose MenC12, 160 participants per group are required for the comparison between the Single Dose MenC-CRM197 and the Two dose MenC groups to detect 10% non-inferiority with a 2.5% level of significance (1-sided), 90% power and allowing for a 12.5% drop-out rate. An additional 114 participants will be required for the Single Dose MenC-TT group to allow a comparison with the Single Dose MenC-CRM197 primed group, allowing for a 12.5% drop-out rate.

No sample size calculation for the alternate limb component of the trial is included as the data generated here will be pilot data.

| Non-inferiority margi | Estimated difference | Power | Sample size required per group | Total sample size required |
| --- | --- | --- | --- | --- |
| 5% | -0.18 | 90% | 526 | 1052 |
|  |  | 80% | 393 | 786 |
| 7.5% | -0.26 | 90% | 253 | 506 |
|  |  | 80% | 190 | 380 |
| **10%** | **-0.35** | **90%** | **140*** | **280** |
|  |  | 80% | 105 | 210 |

** Requires 160 participants per group when allowing for a ‘dropout’ rate of 12.5%*

A previous study has shown the mean (SD) logSBA=2.85 (0.48) at 1 month following a 12 month dose of MenC vaccine with no prior MenC immmunisation43. Making the reasonable assumption that the SBA titres are relatively stable in the one month period after the vaccination, these statistics were used to calculate a sample size for a comparison between the one dose group and 0 dose control group at 6 days after the 12 month vaccination.

To detect a difference of 0.285 (10% of 2.85) between groups of equal size of 56 with a significance level of 0.05 (2-sided), would provide a power of 88%. Allowing for 12.5% drop outs, the initial size of 0 dose control group should be 64 infants. This therefore enables the 6 day blood test to be performed on only a subset of participants (64) in each of the other groups.

***Assumptions***

Sample size calculation has been extrapolated from the following MenC rSBA data taken from the infant MenC study39, at various time points:

12 months

Log10 rSBA : mean= 0.9441395 Std. Dev = 0.8876458

Log10 IgG : mean= 0.02791 Std. Dev = 0.4380407

6 days-post 12 months booster

Log10 rSBA : mean= 3.672566 Std. Dev = 0.2518598

Log10 IgG : mean= 1.211286 Std. Dev.= 0.1606558

8 days-post 12 months booster

Log10 rSBA : mean= 4.264592 Std. Dev = 0.584236

Log10 IgG : mean= 1.72307 Std. Dev.= 0.3447821

30 days-post 12 months booster

Log10 rSBA: mean= 3.784377 Std. Dev = 0.4211916

Log10 IgG: mean= 1.446253 Std. Dev.= 0.3564013

## 9.3 Hypothesis Test

Non-inferiority of Single Dose MenC-CRM197 schedule over Two Dose MenC schedule would be demonstrated if the null hypothesis bellow is rejected.

**Null Hypothesis H0**:

The mean of (log10) of MenC rSBA values of the active current vaccine schedule (Two Dose) group μexp, exceeds the mean of (log10) of MenC rSBA values of the experimental vaccine schedule (Single Dose) group μac by at least a margin “M” (M >0).

**H0**: μexp –μac ≤ -M

**Alternative Hypothesis Ha**: The mean of (log10) of MenC rSBA values of the active current vaccine schedule (Two Dose) may indeed have higher mean of (log10) of MenC rSBA values compared to mean of (log10) of MenC rSBA of the experimental vaccine schedule (Single Dose) group, but the difference is not more than “M” (M >0).

**Ha**: μexp –μac > -M

- μexp refers to the population mean of log10 of MenC rSBA values for the experimental vaccine schedule (Single dose) group
- μac refers to the population mean of log10 of MenC rSBA values of the active current vaccine schedule (Two Dose) group.

For the above comparison, M, the non-inferiority margin, is chosen to be 0.35, this value corresponds to a 10% of the value 3.47 log10 (MenC rSBAGMT) at 1 month after booster (Reference 14, Borrow et al)

μexp and μac can be estimated as log10 (MenC rSBAGMT) in (Single Dose) and (Two Dose) groups respectively (which are equivalent to the arithmetic mean of log10 MenCrSBA in (Single Dose) group and the arithmetic mean of log10 MenCrSBA in (Two Dose) group).

The nominal significance level for this one-sided test is considered α=0.025 and power is 90%.

If the null hypothesis is rejected we can then conclude non-inferiority of the experimental Single Dose priming vaccine schedule compared to Two Dose priming vaccine schedule.

